##### Semistructured Interviews

Information gathered from semistructured interviews with a subsample of study participants will be analyzed using ATLAS.ti software (ATLAS.ti Scientific Software Development GmbH). A multistage standardized thematic analysis will be performed: familiarization with the data, generating preliminary codes, gathering potential themes, reviewing the themes, refining the themes and labeling them, and conducting the write-up of the analysis [107]. Two members of the research team will code the responses for process alignment [108]. In the analysis, we are interested specifically in participants’ experiences with the different types of exercises, in what way these were helpful (or not), and whether participants were able to understand the different approaches and exercises embedded in the intervention (eg, ACT, CD, and self-compassion).

#### Secondary Outcome Analysis

##### Analysis of Distal Outcomes: ER Skills and Distress Symptoms

For estimating the effect of the intervention on participants’ ER skills and levels of distress, we will apply a multiple linear regression model with the following covariates: gender, age, study year, preknowledge of therapeutic approaches, and intervention adherence (ie, number of completed exercises).

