#### Evaluation of the Distal Outcomes of the Intervention

ER skills and level of distress (ie, stress as well as anxiety and depressive symptoms) will be evaluated before and after the intervention period for the purpose of safety monitoring and to inform the design of a follow-up RCT. In terms of safety, the results will be used to indicate whether negative changes in individuals’ MH (ie, distress symptoms) occurred between baseline and the end of the intervention period. As there is no comparator group, the results will provide only an indication of a potential link between worsened (or improved) distress symptoms and the intervention, which will be further tested in a traditional RCT. In terms of RCT design, given the innovative nature of this intervention, there is no prior data available to estimate its effect size. Therefore, we will use the pre-post evaluation of distal outcomes in this study as a pilot evaluation of changes in the distal outcomes to estimate the potential effect size of the intervention. This estimate will be used to calculate the sample size for the standard RCT, where between-group changes in distal outcomes (ie, ER skills and distress symptoms) will be evaluated.

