## Methods

### Study Design

This study uses an explanatory sequential mixed methods approach combining an MRT (phase 1) [22] with follow-up semistructured interviews (phase 2; refer to Figure 1 for an overview). During the MRT, the participants (N=200) will be randomized 2 times per day (morning and evening) to the intervention (ie, an exercise supporting ER; 60% probability) or to a control intervention (ie, a health snippet; 40% probability) over a span of 21 days. Data will be collected at baseline and at the end of the 3-week intervention period, as well as daily via the app before and after the completion of each assigned exercise or health snippet. The primary outcomes include changes in emotional states and engagement patterns with the intervention. For the exercises targeting unhelpful thoughts, differences in thought believability and discomfort before and after the CD exercises will be evaluated. The secondary outcomes include changes in the 4 distal outcomes—ER skills, perceived stress level, and levels of anxiety and depressive symptoms—which will be measured at baseline and at the end of the intervention phase (ie, after 21 days; refer to Table 1 for the measurement schedule).

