#### Secondary Outcomes

ER will be measured with the Emotion Regulation Skills Questionnaire [100], which evaluates 8 types of ER skills: awareness, sensation, clarity, understanding acceptance, tolerance, compassionate self-support, readiness to confront distressing situations, and modification of negative emotions. Each skill is assessed with 3 items rated on a scale ranging from 0 (not at all) to 4 (almost always). Apart from the scores on separate subscales, the Emotion Regulation Skills Questionnaire consists of a total score computed as the average of all items. Higher scores indicate higher ER skills.

Symptoms of depression and anxiety are measured with the PHQ-9 [61] and the Generalized Anxiety Disorder-7 (GAD-7) [101] questionnaire, respectively. The PHQ-9 consists of 9 items measuring depressive symptoms, and the GAD-7 is composed of 7 items measuring anxiety symptoms. Both questionnaires instruct participants to indicate how often they have been bothered by different symptoms over the last 2 weeks on a scale ranging from 0 (not at all) to 3 (nearly every day). The summed scores for the PHQ-9 range from 0 to 27 and for the GAD-7 from 0 to 21, with higher scores indicating higher levels of depressive and anxiety symptoms. The PHQ-9 is used both to screen for eligibility and to assess the baseline level of depression.

Stress levels will be assessed with the Perceived Stress Scale-14 [102], which consists of 14 items and instructs participants to indicate how often they felt or thought a certain way over the last month on a scale ranging from 0 (never) to 4 (very often). The summed scores range from 0 to 56, with higher scores indicating higher levels of perceived stress symptoms (refer to Table 1 for an overview of the measurement schedule).

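### As written, the distal-outcome regression does not isolate the mean change from baseline: its dependent variable is unnamed, it lists no baseline score or pre/post term, and it adjusts for exercises completed during the study

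*Protocol article*

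**What the plan says.** Under Evaluation of the Distal Outcomes of the Intervention, the protocol article gives these outcomes two uses. The first is safety: to indicate "whether negative changes in individuals’ MH (ie, distress symptoms) occurred between baseline and the end of the intervention period". The second is planning: "we will use the pre-post evaluation of distal outcomes in this study as a pilot evaluation of changes in the distal outcomes", and "This estimate will be used to calculate the sample size for the standard RCT". The same section limits what can be concluded, beginning "As there is no comparator group".

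Under Analysis of Distal Outcomes: ER Skills and Distress Symptoms, one analysis is given: "For estimating the effect of the intervention on participants’ ER skills and levels of distress, we will apply a multiple linear regression model". Its covariates are "gender, age, study year, preknowledge of therapeutic approaches, and intervention adherence (ie, number of completed exercises"). That section does not say whether the dependent variable is the day-23 score or the change from baseline.

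Other sections bear on this:
- Study Design: "The secondary outcomes include changes in the 4 distal outcomes".
- Secondary Outcomes: "The PHQ-9 is used both to screen for eligibility and to assess the baseline level of depression". Table 1 has the other three scales on both day 1 and day 23, so paired values are collected for all four outcomes.
- Data Analysis Plan: key baseline variables, with sex as the example, will be considered as covariates. Baseline distal scores are not named.
- Effects of the Intervention on the Proximal Outcomes: the proximal models do adjust for pre-exercise affect scores.

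**The concern.** With no comparator there is no treatment term. The only quantity that can serve the pre-post objective is the mean change from baseline, which must appear as a time coefficient or as the intercept of a change-score model. The stated model has no time term, and its intercept depends on how a variable measured after baseline is coded.

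That leaves the coefficient of completed exercises as the term most likely to be read as the effect of the intervention. Completion is behaviour during the study. It can depend on baseline severity and on how mood develops, and the count also mixes willingness to engage with the 60:40 draw of exercise or health snippet.

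A misread intercept or slope would pass into the sample size of the follow-up RCT. Separately, the stated safety purpose concerns individuals, and no summary of individual worsening is described.

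**Working it through.** The article gives no effect size or power figure for the distal outcomes, so there is none to reproduce. The check is of what each term in the model means.

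**Inputs from the article.** Expected exercises prompted: 42 × 0.6 = 25.2 (Study Procedure). Expected response to prompts: 70% (Participants). Expected exercises completed: 25.2 × 0.7 = 17.6. Participants completing phase 1: 137 (Results).

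**Assumed inputs, to show direction only.** Symptom score with baseline mean 10 and SD 4; pre-post correlation r = 0.6; true mean change −1.0 (improvement); completed exercises SD 5; correlation of completed exercises with baseline severity 0 or −0.3; true slope 0 or −0.1 point per exercise.

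**Reading 1: the outcome is the day-23 score.** The model holds no baseline information. Its intercept is a score level, not a change: in simulation (2,000 replicates, n = 137) it averaged 9.0 to 13.3 across the four scenarios. No term corresponds to −1.0.

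**Reading 2: the outcome is the change score, count not centred.** The intercept is the expected change at zero exercises, that is, mean change − slope × 17.6.
- The slope picks up baseline severity when baseline is not in the model. This contribution is (r − 1) × SD × correlation ÷ 5. With correlation −0.3 it is (−0.4 × 4 × −0.3) ÷ 5 = +0.096.
- Slope −0.1, correlation 0: intercept = −1.0 + 0.1 × 17.6 = +0.76.
- Slope 0, correlation −0.3: intercept = −1.0 − 0.096 × 17.6 = −2.69.

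Simulated averages:

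| True slope | Correlation with baseline | Raw intercept | Intercept, count centred | Slope, change score | Slope, day-23 score | Slope, baseline added |
|---|---|---|---|---|---|---|
| 0 | 0 | −1.01 | −1.00 | 0.00 | 0.00 | 0.00 |
| −0.1 | 0 | +0.76 | −0.99 | −0.10 | −0.10 | −0.10 |
| 0 | −0.3 | −2.70 | −1.00 | +0.10 | −0.14 | 0.00 |
| −0.1 | −0.3 | −0.92 | −0.99 | 0.00 | −0.24 | −0.10 |

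The standard error of the raw intercept is about 1.13, against about 0.31 with the count centred.

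**The slope.** In the third row there is no true dose effect. The slope nevertheless suggests benefit with the day-23 score (−0.14) and harm with the change score (+0.10). In the fourth row the change score hides a true slope of −0.1. Adding the baseline score removes this source of bias. It does not remove confounding by how mood develops during the three weeks.

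**Precision.** With equal variances, the standard error of the mean change is SD × √(2(1 − r)/n) for a paired change score and for the time term of a mixed model alike, so neither gains over the other. For covariate slopes, residual variance is 2(1 − r)SD² with a change score and (1 − r²)SD² with baseline adjusted. The ratio of standard errors is √(2/(1 + r)): 1.15, 1.12 and 1.08 for r = 0.5, 0.6 and 0.7 (assumed).

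**Individual worsening.** The SD of change is 4 × √(2 × 0.4) = 3.58. Taking a rise of 5 points purely as an illustration, the standardised distance is (5 + 1) ÷ 3.58 = 1.68, a probability of about 4.7% (4.5% to 4.9% in simulation). The mean improves by 1 point throughout, and no regression coefficient shows those participants.

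**The case against.** The strongest reply is that the article repeatedly calls the distal outcomes changes, in the objective, in Study Design and in the Discussion. Under a change-score reading, baseline enters through the outcome. Centring or marginal prediction, both routine, then recovers the mean change exactly. Age is also in the covariate list, so nobody would report the raw intercept as the estimate in any case. This largely stands. A reader might infer that the plan cannot estimate the pre-post change. The documents do not support that: it is not estimated as written, but it can be. What remains is that the analysis section states a specific covariate list, names neither the outcome nor the centring, and includes a post-baseline count in a model said to estimate the intervention effect.

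Two further inferences are tempting but unsupported:
- That omitting baseline widens intervals by 15–40%. The formula 1/√(1 − r²) applies to slopes in a day-23-score model, not to the mean change. With no comparator there is no treatment contrast for it to apply to.
- That both time points would be analysed as independent rows. Nothing in the article says so.

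On individual worsening, the objection is fair that no mean model shows it, including a mixed model, and that descriptive statistics are planned for all variables. It is therefore a separate summary to add, not a fault of this regression alone. The article also limits its safety claim to an indication of a potential link.

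**Conclusion.** The point holds as a specification defect in a secondary, uncontrolled analysis. Under the day-23-score reading, no term is the mean change. Under the change-score reading, the raw intercept differs from the mean change by 17.6 times the slope of completed exercises, which is 1.76 points for an assumed slope of 0.1. That discrepancy vanishes if the count is centred or removed. Under either reading, the coefficient of completed exercises is not an intervention effect, and without the baseline score its sign can depend on which outcome is chosen.

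The simulated values rest on assumed variances, correlations and slopes and show direction only. The reasoning about what each term means does not depend on them. The primary proximal analysis is not affected.

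**What to change.** - State the dependent variable, and state that the pre-post change is estimated from the paired data. Use either a mixed model with a time term (baseline, day 23) and a random participant intercept, or a change score with centred baseline covariates. Leave completed exercises out of this model.
- If the association with completed exercises is reported, put it in a separate exploratory model that adjusts for the baseline score, and label it non-causal.
- For the safety purpose, report the number and percentage of participants who worsened on the PHQ-9, GAD-7 and Perceived Stress Scale, using a definition set in advance, and show missing day-23 data beside it. Results gives 161 participants and 137 completing phase 1, so up to 161 − 137 = 24 (14.9%) may lack a day-23 score if phase 1 completion includes that questionnaire.

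The cost is analysis wording; all the data are already collected. Because data collection has ended and analysis is under way, date the clarification and state whether distal results had been seen.

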##### Analysis of Exploratory Outcome Analysis: Contextual Moderators

For the purposes of optimization of the mobile intervention app, exploratory analyses will be carried out to explore contextual factors, that is, the time of intervention delivery (morning vs evening), momentary emotional state, and vulnerability to MH problems indicated by higher scores on the GHQ-12, as potential moderators of perceived helpfulness and of the proximal effects on changes in emotional states among the intervention and intervention categories. Additional exploratory variables of interest include personality traits and gender. This information will help us form initial decision rules for the algorithm that is being designed for this intervention.

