#### Intervention Optimization Using an MRT Method

To design an adaptive system of interventions responsive to users’ needs, the optimization of their contents and delivery is crucial. This study will combine an MRT with user experience interviews, a novel study design that can provide information on which intervention is effective for whom and in what context [30].

An MRT can evaluate how different intervention components affect an individual in real time (ie, directly after they have used it), and it assesses how this effect varies over time (eg, an intervention may be effective at the beginning, but its effectiveness may decrease with time). In addition, this method can evaluate the moderating role of contextual factors (eg, current mood or the time of day) on the intervention effect, which is especially helpful when optimizing rules for intervention delivery [50,51]. Although it is a young method, an MRT has been successfully applied to evaluate dynamic and user-tailored eHealth interventions focused on weight management [52], smoking cessation [53], and MH [54]. Within the field of MH, NeCamp et al [55] investigated the optimal timing for delivering a mobile MH intervention to medical interns. The authors found that delivering an intervention when individuals experienced lower levels of MH indicated by low mood, poor sleep, and reduced activity was beneficial, whereas intervening when the individuals were doing well had a negative effect [55]. Another MRT study evaluated the impact of an ACT-based mobile intervention on distress symptoms (ie, depressive and stress symptoms) in first-generation university students [56], and the results suggest that interventions prompting mindful awareness and acceptance of internal experience (ie, thoughts, emotions, and physical sensations) were the most impactful for decreasing depressive symptoms. In addition, interventions delivered in the evening were more predictive of decreases in distress symptoms than those delivered in the morning [56]. Both studies signal the importance of considering contextual factors to optimize the impact of digital MH interventions.

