Using MRT research design allows for the gathering of more granular and proximal insights about a given intervention, which cannot be captured through traditional RCT designs. In an MRT, unlike in a traditional RCT where individuals are randomized to an intervention or control group at the beginning of the trial, different intervention components (or no intervention) are repeatedly randomized to the participants at prespecified decision points. Thus, in an MRT, the randomization unit is not the participant but the intervention, and participants act as their own controls. Therefore, compared with an RCT, which focuses on between-participant effects, the MRT measures within-participant effects aggregated across participants. The decision point refers to the time of day at which an individual may or may not receive an intervention. Furthermore, the proximal outcome refers to the short-term goals of the intervention (ie, intervention targets) and is seen as the facilitator of the desired distal outcome of the intervention (ie, a mediator of the long-term outcome); for example, if the focus of an intervention is on increasing physical activity, a proximal outcome would be the number of steps taken within 30 minutes after an intervention was delivered, and the distal outcome would be the overall increase in physical activity at the end of the entire intervention period [51].

Finally, owing to repeated randomization, an MRT allows for the evaluation of the moderating role of contextual factors, such as current mood and time, on the proximal effects of the intervention [22].

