#### Exploratory Goal: The Impact of Contextual Moderators on Proximal Intervention Effects

The role of the time of day, momentary emotional state, personality type, preferences, and intervention type as moderators will be explored to determine the context under which the intervention and its categories exercises are the most effective.

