### Outcome Measures

#### Primary Outcomes

##### Changes in a Momentary Emotional State

Participants will be asked to evaluate 7 emotional states by answering the question “How [*affect*, eg, happy] do you feel at the moment?” on a scale ranging from 1 (not at all) to 5 (very much). The emotional states are combined into 2 categories of affect: negative (stressed, frustrated, sad, and fatigued) and positive (happy, energetic, and relaxed) [98]. The scores of the emotional states will be averaged per category for preintervention and postintervention EMA assessment. The 2 composite outcomes will be calculated by subtracting the results of the preintervention EMA from those of the postintervention EMA for the positive affect and negative affect categories.

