Compared with other methodologies used for intervention evaluation such as an RCT, the MRT design makes it possible to observe proximal changes in participants’ emotional states directly after they complete an exercise, in addition to requiring fewer participants to achieve sufficient power to detect the proximal main effect of an intervention component [52]. This enables insight into the mechanisms of change (ie, changes in emotional states), elucidating on how the intervention and its components stimulate the desired benefits (ie, increase in ER skills and decrease in depressive and anxiety symptoms). Combining results from the MRT with information on user engagement patterns (ie, log data analytics) and user experience (ie, exercise ratings and user experience interviews) will help unpack the black box typical of studies of digital MH interventions, where often little is known about the mechanisms by which the interventions exert their benefit [109]. The combined results will also indicate intervention components that might need improvements or should be discarded when they play no significant, or possibly impeding, role in facilitating the desired change. This means that if an intervention category is perceived as unhelpful, unlikable, or unclear or was hardly used by participants, and when it was used, it showed a negative or no effect on proximal outcomes, the intervention category (or specific exercises) could be removed from the intervention library or redesigned. Furthermore, the use of a mixed methods approach not only offers the opportunity to gather valuable insight into how the current generation of students perceive and engage with digital MH interventions but also sheds light on how they receive the MRT as a method of evaluation. This information can help optimize future endeavors in the development and evaluation of tools for digital MH interventions. Finally, the results of exploratory analyses and the data set obtained in this study will be used to develop and train the recommendation algorithm, maximizing the likability and usefulness of exercises for users based on individual (ie, personality and MH status) and contextual (eg, the time of day and momentary emotional states) characteristics. Creating a system that can suggest content relevant to its users has been indicated as a top priority for university students to engage and remain engaged in an MH app [18]. Therefore, designing and implementing a recommendation system in the app may be crucial in improving its uptake and effectiveness.

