Third, our mobile app combines various types of exercises based on different therapeutic approaches ranging from self-compassion to positive psychology. The exercises were designed in such a way that they can be completed in the moment, without users’ preknowledge of the approach. In this study, we offer them materials educating them about the underlying exercise approach, but this is kept optional. There is a possibility that some exercises might be more effective when presented in combination with psychoeducational material. In addition, given the randomized nature of the exercises, participants might find some suggestions less appropriate when reporting certain states (eg, recommending an exercise belonging to the upregulation of positive affect category when participants report a high-stress state). However, the experimental goal of the study is to empirically examine how the exercises affect participants’ emotional states and participants’ reactions to the exercises (whether they like them or find them helpful) instead of drawing conclusions based on current psychological theories and our hunches. Current psychological theories seem to be insufficient to inform the development of mobile interventions that include high levels of interactivity and flexibility. This is because prevailing behavior change theories are still based on data providing information on static snapshots of behavior (ie, the predictions of behavior are based on pre-post evaluations) rather than accounting for contextualized and transitory changes in mood states and behavior at the granular level [112-114]. However, an MRT can address the limitations of traditional research methods, such as RCTs, which have shaped current behavior change theories. Specifically, an MRT offers a deeper understanding of the dynamics involved in health behaviors and behavior change, which are influenced by a myriad of contextual factors, including emotional states, physical context, social norms, and expectations [115]. These factors seem to play a role in intervention functioning [51,55,56]. Therefore, with this study, we hope to gather insights and draw experimentally informed conclusions regarding which intervention option is appropriate for whom and in what context.

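### Momentary emotional state, planned as a contextual moderator, blends a student's usual level with the momentary deviation; adding a two-part model would separate 'for whom' from 'when'

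*Protocol article*

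**What the plan says.** All references are to the protocol article.

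- **Definition of the score** (Changes in a Momentary Emotional State): seven states are rated 1 to 5 and grouped into negative and positive affect. "The scores of the emotional states will be averaged per category for preintervention and postintervention EMA assessment". Nothing there relates a score to the student's own average.
- **Moderator analysis** (Contextual Moderators): "exploratory analyses will be carried out to explore contextual factors, that is, the time of intervention delivery (morning vs evening), momentary emotional state". GHQ-12 vulnerability is listed with these, and personality traits and gender are named as further variables of interest.
- **Use of the result** (same section): "This information will help us form initial decision rules for the algorithm that is being designed for this intervention".
- **How the score is classed** (Discussion, Overview): the recommendation algorithm is to work "based on individual (ie, personality and MH status) and contextual (eg, the time of day and momentary emotional states) characteristics". Momentary state therefore sits on the contextual side, apart from the individual characteristics.
- **Aim** (Exploratory Goal): "to determine the context under which the intervention and its categories exercises are the most effective". The section on the MRT method promises "information on which intervention is effective for whom and in what context", and Limitations repeats the aim as "which intervention option is appropriate for whom and in what context".
- **What the design is said to measure** (MRT method section): "the MRT measures within-participant effects aggregated across participants".

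The primary analysis section names weighted and centered least squares and refers to Multimedia Appendix 4 for detail. That appendix is not shown. The centering in the method's name concerns treatment, not the moderator.

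**The concern.** A rating taken before the exercise answers two questions at once: how this student generally feels, and how the student feels now compared with that. Treatment can interact with either part. Suppose habitually distressed students gain more from an exercise, while for any one student it makes no difference whether the moment is good or bad. A single interaction with the score will still tend to be positive, and because the score is labelled contextual, it invites the conclusion that distressed moments are the better ones for an exercise.

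Randomization does not remove this. It makes the draw independent of the score, so the moderated effect is estimated without bias at each score value. It does not show which part of the score carries the moderation.

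The distinction matters because the article wants both answers and will build on them. A recommendation system can match content to a student or respond to a student's moment, and these are different rules.

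**Working it through.** The article gives no figure on this point, so there is none to reproduce. The check is a formula and a simulation.

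**Inputs from the document**
- Decision points per student: 42. Assumed response: 70%. So 42 × 0.70 = 29.4 answered points, taken as 29.
- Probability of an exercise: 0.6 at every draw, whatever the state.
- Students: 137, the number who completed the first phase.

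**Assumptions not in the document**
- Score with unit variance; between-student share of that variance ρ from 0.2 to 0.6.
- Moderation slopes b_B (usual level) and b_W (momentary deviation) of 0 or ±0.2 residual SD per unit of score; residual SD 1.

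**Formula.** Write the score as S = u + w, with u the usual level (variance ρ) and w the deviation (variance 1 − ρ). If the treatment effect is linear in u and w, the slope on S alone is

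raw slope ≈ ρ·b_B + (1 − ρ)·b_W.

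**Simulation.** Treatment centered at 0.6, participant-clustered sandwich standard errors, 400 runs per setting. The split model here uses the student's mean over all answered points and the deviation from it.

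| ρ | b_B | b_W | Formula | Simulated raw slope | Raw slope significant at .05 | Simulated within slope after split |
|---|---|---|---|---|---|---|
| 0.2 | 0.2 | 0 | 0.04 | 0.040 | 21% | 0.001 |
| 0.4 | 0.2 | 0 | 0.08 | 0.079 | 61% | 0.001 |
| 0.6 | 0.2 | 0 | 0.12 | 0.118 | 89% | −0.002 |
| 0.2 | 0.2 | −0.2 | −0.12 | −0.121 | 94% | −0.200 |
| 0.4 | 0.2 | −0.2 | −0.04 | −0.041 | 19% | −0.199 |
| 0.6 | 0.2 | −0.2 | 0.04 | 0.036 | 18% | −0.198 |
| 0.2 | 0 | 0.2 | 0.16 | 0.163 | >99% | 0.203 |
| 0.4 | 0 | 0.2 | 0.12 | 0.122 | 94% | 0.203 |
| 0.6 | 0 | 0.2 | 0.08 | 0.080 | 62% | 0.202 |

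- **Rows 1 to 3 (no momentary moderation):** the raw score is often significant, while the within term of the split model is significant in 5 to 6% of runs, about its nominal level.
- **Rows 4 to 6 (opposite slopes):** the raw slope keeps the within-student sign at shares 0.2 and 0.4 and reverses at 0.6. By the formula, reversal needs ρ/(1 − ρ) > |b_W|/b_B. For equal and opposite slopes that means ρ > 0.5.
- **Rows 7 to 9 (momentary moderation only):** the raw slope understates the true 0.2.

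**With a mean of earlier scores only.** This version uses nothing later than the current draw. With b_B = 0.2, b_W = 0 and shares 0.3 to 0.6, the raw interaction was significant in 39 to 96% of runs and the momentary term of the split in 6 to 8% (7 to 9% with autocorrelation 0.4 between successive states).

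The small excess over 5% has a clear source: a mean of few scores measures the usual level imperfectly. With k earlier scores and no autocorrelation, the deviation term picks up b_B / [(1 − ρ)/ρ + k + 1]. At ρ = 0.4 and b_B = 0.2 this is 0.2/5.5 = 0.036 for k = 3 and 0.2/17.5 = 0.011 for k = 15, against 0.08 for the raw score.

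**The case against.** - **The raw-score slope is a legitimate estimand.** This stands. With 60:40 draws at every state, it is a population-average excursion effect given the observed score. A rule keyed to that score is right on average, though it may be less efficient than one using both parts. A reader might infer that the planned analysis is biased; it is not. The fault arises only if the slope is read as a statement about moments within a student, and the contextual label invites that reading.
- **The article does not say the score will be entered unsplit.** This also stands. A reader might infer that the investigators have ruled out a split. The text shown lists candidate moderators without a model, and Multimedia Appendix 4 could contain more. The point therefore rests on the definition, the label and the intended use taken together, not on silence alone.
- **Person-level moderators are already listed.** GHQ-12, personality and gender are there, but GHQ-12 is a single baseline questionnaire, not the student's average momentary affect. Nothing says that any of them enters the same model as momentary state.
- **The size is assumed.** This stands. The 0.2 slope is twice the average effect of 0.1 in the sample size section, and pairing it with exactly zero momentary moderation is a constructed case. A reader might infer that a wrong-way rule is likely. Nothing in the document makes the required combination of share and slopes probable.
- **The analysis is exploratory, its rules are initial, and an RCT of the optimized app follows.** This limits the severity. It does not remove the point, because that RCT would test an app already shaped by these rules.

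**Conclusion.** The concern holds as an improvement to an exploratory analysis. The score as defined mixes usual level and momentary deviation, the article treats it as contextual and passes the result to decision rules, and the text shown separates nothing. One interaction with that score is valid as a population average but cannot tell who benefits from when they benefit.

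How far it would mislead is unknown. Under the assumed between-only moderation of 0.2 the raw term is significant in about one run in five at a share of 0.2 and about nine in ten at 0.6. A sign reversal needs opposite slopes and a large enough share. These figures depend on shares and slopes that the document does not give. The primary analysis of proximal effects is unaffected.

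**What to change.** In the exploratory moderator analysis, keep the raw-score moderator and add a second model with two treatment interactions, for positive and for negative affect:

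1. the mean of the student's pre-exercise scores from earlier answered slots, using only information before the current draw;
2. the current pre-exercise score minus that mean.

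Interpret the second term when deciding on moment-based suggestions and the first when matching content to students. State this coding and reading with the moderator analysis. Both terms are known before the draw, so they fit the planned weighted and centered least squares method, and no new data are needed.

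Costs: early slots have little or no history, and dropping the first three answered slots loses 3/29.4, about 10% of draws. The momentary term is less precise than the raw-score term. Slight mixing remains while the running mean rests on few scores.
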